[figure not shown][figure not shown][figure not shown]

## GENERAL INFORMATION

This document describes the PIVOT trial and provides information about procedures for entering patients into the trial. The protocol should not be used as an aide-memoire or guide for the treatment of other patients; every care was taken in its drafting, but corrections or amendments may be necessary. These will be circulated to the registered investigators in the trial, but centres entering patients for the first time are advised to contact the HIV Group, Medical Research Council Clinical Trials Unit, London to confirm they have the most up-to-date version. Clinical problems relating to this trial should be referred to the Chief Investigator.

- **Compliance**

The trial will be conducted in compliance with the protocol, MRC GCP, Data Protection Act (DPA number: Z5886415), NHS research governance and other regulatory requirements, as appropriate in the participating centres.

- **Sponsor**

Medical Research Council, [name].

- **Funder**

NHS R&D Health Technology Assessment (HTA) Programme, [name], UK.

 APPENDIX 15: PROTOCOL VERSION 4.0 LISTING OF CHANGES  
 APPENDIX 16: PATIENT INFORMATION SHEET – EXTENSION PHASE  
 APPENDIX 17: CONSENT FORM – EXTENSION PHASE

## ABBREVIATIONS AND GLOSSARY

|                |                                                      |
|----------------|------------------------------------------------------|
| AE      | Adverse event                                        |
| ACTG    | AIDS Clinical Trials Group                           |
| AIDS    | Acquired immune deficiency syndrome                  |
| ALT     | Alanine transaminase                                 |
| AR      | Adverse reaction                                     |
| ART     | Antiretroviral therapy                               |
| AST     | Alanine aminotransferase                             |
| BHIVA   | British HIV Association                              |
| BNF     | British National Formulary                           |
| CCR5    | Chemokine (C-C motif) receptor 5                     |
| CDC     | Center for Disease Control and prevention            |
| CDSC    | Communicable Disease Surveillance Centre             |
| CHM     | Commission on Human Medicine                         |
| CF      | Consent form                                         |
| CG      | Cockcroft-Gault equation                             |
| CI      | Chief Investigator                                   |
| CRF     | Case Report Form                                     |
| CT      | Computerised (Axial) Tomography scan                 |
| CTA     | Clinical Trials Authorisation                        |
| CTU     | Clinical Trials Unit                                 |
| DoH     | Department of Health                                 |
| ECG     | Electrocardiogram (also EKG)                         |
| EDTA    | Ethylenediaminetetraacetic acid                      |
| ELISA   | Enzyme-Linked ImmunoSorbent Assay                    |
| EQ-5D   | Euroqol (five-domain) health status questionnaire    |
| ERC     | Endpoint Review Committee                            |
| EUDRACT | European Union Drug Regulatory Agency Clinical Trial |
| GP      | General Practitioner                                 |
| HAART   | Highly Active Antiretroviral Therapy                 |
| HDL     | High-density lipoprotein                             |
| HE      | Health Economics                                     |
| HIV     | Human Immunodeficiency Virus                         |
| HTA     | Health Technology Assessment                         |
| IB      | Investigator's Brochure                              |
| HVLT-R  | Hopkins Verbal Learning Test – revised               |

|                |                                                                  |
|----------------|------------------------------------------------------------------|
| ICH GCP | International Conference on Harmonisation Good Clinical Practice |
| IDMC    | Independent Data Monitoring Committee                            |
| IMP     | Investigational Medicinal Product                                |
| ISRCTN  | International standard randomised controlled trial number        |
| ITT     | Intention to treat                                               |
| KS      | Kaposi's sarcoma                                                 |
| LDL     | Low-density lipoprotein                                          |
| LFT     | Liver function tests                                             |
| LREC    | Local research ethics committee                                  |
| MHRA    | Medicines and Healthcare Regulatory Authority                    |
| MHS     | Mental health summary score                                      |
| MI      | Myocardial infarction                                            |
| MOS HIV | Medical Outcomes Study HIV Health Survey                         |
| MRC     | Medical Research Council                                         |
| MRI     | Magnetic resonance imaging                                       |
| NARS    | Neuropsychiatric AIDS Rating Scale                               |
| NHS     | National Health Service                                          |
| NRTI    | Nucleoside reverse transcriptase inhibitors                      |
| NNRTI   | Non-nucleoside reverse transcriptase inhibitors                  |
| OT      | On-treatment                                                     |
| PHS     | Physical health summary score                                    |
| PI      | Protease Inhibitor                                               |
| PIS     | Patient Information Sheet                                        |
| QALY    | Quality-adjusted life-year                                       |
| QoL     | Quality of Life                                                  |
| R&D | Research and Development                                         |
| REC     | Research Ethics Committee                                        |
| RNA     | Ribonucleic acid                                                 |
| SAE     | Serious adverse event                                            |
| SAR     | Serious adverse reaction                                         |
| SD      | Standard deviation                                               |
| SOP     | Standard operating procedure                                     |
| SmPC    | Summary of product characteristics                               |
| SUSAR   | Suspected unexpected serious adverse reaction                    |
| TLOVR   | "Time to loss of virologic response"                             |
| TDM     | Therapeutic drug monitoring                                      |
| TMG     | Trial Management Group                                           |
| TSC     | Trial Steering Committee                                         |
| UAR     | Unexpected adverse reaction                                      |
| UEC     | Urea, Electrolytes and Creatinine                                |
| UK-CAB  | United Kingdom Community Advisory Board                          |
| ULN     | Upper limit of normal                                            |
| VL      | Viral load                                                       |
| WCC     | White cell count                                                 |

# 1. SUMMARY

## 1.1 Background and Aims

The current standard-of-care treatment for people living with HIV is combination antiretroviral therapy (ART), usually consisting of 3 drugs: 2 nucleoside reverse transcriptase inhibitors (NRTIs) with either a non-nucleoside reverse transcriptase inhibitor (NNRTI) or a protease inhibitor (PI). Although triple ART has a relatively high long-term success rate, a proportion of patients (about 4% per year) continues to experience virological failure, and this is often associated with complete resistance to one or more drugs (especially NRTI and NNRTI classes). Furthermore, long-term drug toxicity remains a concern. Additional strategies for long-term management are needed that preserve future drug options and minimise toxicity. Short-term clinical trials suggest that stable patients who have had prolonged virological suppression on combination ART can be switched successfully to PI monotherapy, resulting in a reduction of toxicity without increasing the risk of treatment failure and drug resistance.

This trial aims to determine whether a strategy of switching to PI monotherapy is non-inferior to continuing triple-therapy, in terms of the proportion of patients who maintain all the drug treatment options that were available to them at baseline after at least 3 years of follow-up, and to compare clinical events, safety, toxicity and health economic parameters between the two strategies.

### 1.1.1 Trial design

This is a parallel group, open-label, multi-centre, randomised controlled strategy trial.

### 1.1.2 Patients to be included

560 patients will be included who are HIV-infected adults on a stable ART regimen of two NRTIs and one NNRTI or PI. Patients will have CD4+ T-cell counts greater than 100 cells/ $\mu$ L, and viral load (VL) less than 50 copies/ml for no less than 6 months. Patients who have had virological failure on any previous ART regimen, who have PI resistance mutations, or in whom PIs are contraindicated will not participate. For more details refer to section 4.

### 1.1.3 Trial interventions – research and control arm

Patients randomised to the PI monotherapy group will stop other ART drugs and start or continue only on a ritonavir-boosted PI (selection of drug at discretion of physician and patient). Those who do not maintain complete virological suppression or who are unable to tolerate the PI (substitution for toxicity is allowed), will promptly switch back to their previous triple-therapy. Patients randomised to the control group will continue their current regimen. For more details refer to section 6.

### 1.1.4 Duration of trial

The trial will be conducted over 5 years, including an initial recruitment period estimated to last 12 to 18 months. All patients will continue on treatment and follow-up until close of the trial. Following the last trial visit, an extension phase will continue for up to a further 5 years in which basic treatment and clinical outcome data will continue to be collected by means of an annual retrospective review of the patients' case notes. For more details refer to section 7.

### 1.1.5 Outcome measures

Analyses will compare the 2 groups by intention to treat (ITT).

**Primary outcome measure:**

Loss of future drug options defined as the occurrence of intermediate to high level resistance to any one or more of the standard antiretroviral drugs (limited to licensed drugs in contemporary use) to which the patient's virus was considered to be sensitive at trial entry.

**Secondary outcome measures:**

- Serious drug\* or disease-related complications
- Adverse events\*
- Virological rebound
- CD4+ count change
- Health-related Quality of Life change\*
- Neurocognitive function change\*
- Cardiovascular risk change\*
- Health care costs\*

\* = not evaluated during the extension phase

For more details refer to section 9.

**1.1.6 Data recorded directly on CRFs**

Clinical and routine laboratory data will be recorded on case report forms (CRFs). A copy will be faxed or sent to the MRC CTU for data entry and the original will be kept at the local centre. For more details see section 7.

**1.1.7 Organisation**

Sponsor: Medical Research Council, UK.

Funder: NHS R&D Health Technology Assessment (HTA) programme, UK.

Coordinator: Medical Research Council Clinical Trials Unit, UK.

**1.2 Flow diagram**

**Figure 1: Trial entry, randomisation and treatment**

[figure not shown]

### 1.3 Trial schedule

| PIVOT trial schedule                                     | Screening
-4wks to Day 0 | Day 0
(Baseline) | PI monotherapy arm only |                   | Week 12
-2/+6 wks | Subsequent
12-weekly visits
Wk 24, 36 etc
±6 wks | Annual visits
Wk 48, 96, 144, 192,
240 and final visit 
± 6 wks |
|----------------------------------------------------------|-----------------------------|---------------------|-------------------------|-------------------|----------------------|-----------------------------------------------------------|--------------------------------------------------------------------------------------|
|                                                          |                             |                     | Week 4
± 2 wks       | Week 8
± 2 wks |                      |                                                           |                                                                                      |
| Complete and sign Consent Form                           | X                           |                     |                         |                   |                      |                                                           |                                                                                      |
| Medical and drug history                                 | X                           | X                   |                         |                   |                      |                                                           |                                                                                      |
| Assessment of drug adherence                             |                             | X                   | X                       | X                 | X                    | X                                                         | X                                                                                    |
| Concomitant medication                                   |                             | X                   | X                       | X                 | X                    | X                                                         | X                                                                                    |
| Symptom review/ physical examination                     | X                           | X                   | X                       | X                 | X                    | X                                                         | X                                                                                    |
| Assessment of clinical adverse events                    |                             | X                   | X                       | X                 | X                    | X                                                         | X                                                                                    |
| Cardiovascular risk assessment                           | X                           |                     |                         |                   |                      |                                                           | X                                                                                    |
| ECG (within last 6 months acceptable)                    | X                           |                     |                         |                   |                      |                                                           |                                                                                      |
| Assessment of healthcare resource utilisation            |                             |                     | X                       | X                 | X                    | X                                                         | X                                                                                    |
| EQ-5D health status questionnaire                        |                             | X                   | X                       | X                 | X                    | X                                                         | X                                                                                    |
| Neurocognitive assessment                                |                             | X                   |                         |                   | X                    |                                                           | X                                                                                    |
| MOS-HIV questionnaire                                    |                             | X                   |                         |                   | X                    |                                                           | X                                                                                    |
| HIV viral load                             | X                           | X                   | X                       | X                 | X                    | X                                                         | X                                                                                    |
| CD4+ count                                               | X                           | X                   |                         |                   | X                    | X                                                         | X                                                                                    |
| Full blood count, UEC and LFTs               | X                           | X                   | X                       |                   | X                    | X                                                         | X                                                                                    |
| Bone profile                                 | X                           |                     |                         |                   | X                    | X                                             | X                                                                                    |
| Glucose and lipids (fasting)                 | X                           |                     | X                       |                   | X                    |                                                           | X                                                                                    |
| Hepatitis B/C serology (within last 6 months acceptable) | X                           |                     |                         |                   |                      |                                                           | X                                                                                    |
| Plasma sample for storage                    | X                           | X                   | X                       |                   | X                    |                                                           | X                                                                                    |
| PI drug concentration                        |                             |                     | X                       | X     | X        |                                                           |                                                                                      |
| Urine protein/creatinine ratio               | X                           |                     |                         |                   | X                    | X                                             | X                                                                                    |
| Urine sample for storage                                 | X                           |                     |                         |                   |                      |                                                           | X                                                                                    |
| Pregnancy test  Urine sample for storage     | X                           |                     |                         |                   |                      |                                                           |                                                                                      |
| Completion of CRF                                        | X                           | X                   | X                       | X                 | X                    | X                                                         | X                                                                                    |

- 1 HIV viral load will be repeated on the same lab sample for any value  $\geq 50$  copies/ml. If  $\geq 50$  copies/ml confirmed on lab re-test, patient will be telephoned for adherence counselling and asked to return for repeat VL test at 4 weeks (window up to 8 weeks) after the first test. Repeat plasma sample for storage will be obtained at the second visit.
- 2 Resistance testing will be performed on a stored sample at the local laboratory in the event of 2 consecutive VL values  $\geq 50$  copies/ml.
- 3 FBC will include Hb, WCC, neutrophil count, lymphocyte count, platelets; UEC will include sodium, potassium, urea, creatinine; LFTs will include bilirubin, ALT, alkaline phosphatase.
- 4 Bone profile (calcium and phosphate) and urine protein/creatinine ratio will be performed at screening, Week 12 and annual visits in all, but quarterly only in those patients taking tenofovir.
- 5 Lipids will include total cholesterol, triglycerides, LDL, HDL. If elevated at Week 12, additional fasting lipid tests can be performed between the annual visit checks as needed to inform clinical management.
- 6 Blood sample will be stored at screening (2X4ml EDTA), Baseline, Week 12 and annual visits (1X4ml EDTA) plus any visit where a second VL sample is taken for confirmation of rebound (2X4ml EDTA).
- 7 PI drug concentration measurement can be repeated at Week 8 and/or Week 12 if Week 4 concentration is low (only in the PI monotherapy arm).
- 8 Pregnancy test in women only; can be urine or blood test, as per standard practice at site; repeated at any subsequent visits where pregnancy is suspected.
- 9 The final visit will be scheduled within 12 weeks before the common closing date of the trial.

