## 7. ASSESSMENTS & FOLLOW-UP

### 7.1 Routine Follow-up

The main part of the trial will run for 5 years, with recruitment being completed within the first 12-18 months. All patients will continue follow-up visits to a common closing date. After this final visit, data on a few key parameters will continue to be collected by annual retrospective review of the patients' routine clinic visit records for a period of up to 5 years.

The assessments are listed in the trial schedule (see section 1.3). Trial visits and assessments will correspond closely to routine clinical care, with 12-weekly visits throughout the trial. Patients randomised to the PI monotherapy arm will have additional visits at Week 4 and Week 8. Additional visits for VL testing will be required at 4-12 weeks following any VL result  $\geq 50$  copies/ml (see section 7.1.6). Data will be entered on the CRF at each visit.

#### 7.1.1 Week 4

This visit is only required for patients randomised to the ***PI monotherapy arm***.

The visit window is  $\pm 2$  weeks from the target visit date. The visit will be scheduled to occur in the morning due to the requirement for fasting blood tests. Patients should be instructed to not eat or drink anything (except plain water) from midnight before the visit. They should be instructed not to take any morning dose of PI medication (other medication can be taken) until after the blood has been drawn. The following assessments will be performed:

- Review of symptoms
- Review of concomitant medications
- Adherence to ART (no. of missed doses in previous 2 weeks and since last visit)
- Targeted physical examination (as needed to evaluate reported symptoms)
- Review of healthcare resource utilisation since last visit (patient self-report and review of case sheet)
- EQ-5D health status questionnaire
- Laboratory tests:
  - HIV viral load
  - Full blood count (haemoglobin, white cells, neutrophils, lymphocytes and platelets)
  - Biochemistry (sodium, potassium, urea, creatinine, bilirubin, ALT, alkaline phosphatase)
  - Fasting glucose
  - Fasting lipids (total cholesterol, triglycerides, LDL, HDL)
  - PI drug concentration (trough level preferred, or at least 4 hours from last dose)
  - Plasma storage (1 X 4ml EDTA sample)

#### 7.1.2 Week 8

This visit is only required for patients randomised to the ***PI monotherapy arm***.

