#### **7.1.4 Subsequent 12-weekly visits (excluding “annual” visits and final trial visit)**

These visits are required for ***all patients***.

The visit windows are  $\pm 6$  weeks from the target visit date. There is no requirement for fasting or drug scheduling for these visits. The following assessments will be performed:

- Review of symptoms
- Review of concomitant medications
- Adherence to ART (no. of missed doses in previous 2 weeks and since last visit)
- Targeted physical examination (as needed to evaluate reported symptoms)
- Review of healthcare resource utilisation since last visit (patient self-report and review of case sheet)
- EQ-5D health status questionnaire (self-completed by patient)
- Laboratory tests:
  - HIV viral load
  - CD4+ count
  - Full blood count (haemoglobin, white cells, neutrophils, lymphocytes and platelets)
  - Biochemistry (sodium, potassium, urea, creatinine, bilirubin, ALT, alkaline phosphatase)
  - Bone profile (calcium and phosphate; only required for patients taking tenofovir)
  - Urine protein / creatinine ratio (only required for patients taking tenofovir)

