#### **7.1.5 “Annual” visits (week 48, 96, 144, 192, 240) and final trial visit**

These visits are required for ***all patients***.

The visit windows are  $\pm 6$  weeks from the target visit date. Patients should be instructed to not eat or drink anything (except plain water) from midnight before the visit. The following assessments will be performed:

- Review of symptoms (including specific questions about neuropathy and body fat changes)
- Review of concomitant medications
- Adherence to ART (no. of missed doses in previous 2 weeks and 3 months)
- Targeted physical examination (as needed to evaluate reported symptoms; at this visit will include measurement of blood pressure, body weight, waist and hip-circumference and assessment of facial lipoatrophy; the final trial visit will also include an assessment of peripheral neuropathy)
- 10-year cardiovascular risk assessment
- Neurocognitive assessment
- Review of healthcare resource utilisation since last visit (patient self-report and review of case sheet)
- EQ-5D health status questionnaire (self-completed by patient)
- MOS-HIV quality of life questionnaire (self-completed by patient)
- Laboratory tests:
  - HIV viral load
  - CD4+ count
  - Full blood count (haemoglobin, white cells, neutrophils, lymphocytes and platelets)
  - Biochemistry (sodium, potassium, urea, creatinine, bilirubin, ALT, alkaline phosphatase)

- Bone profile (calcium and phosphate; required for all patients at this visit)
- Fasting glucose
- Fasting lipids (total cholesterol, triglycerides, LDL, HDL)
- Hepatitis B and C serology (if clinically indicated)
- Plasma storage (1x 4ml EDTA at annual visits; 2x 4ml EDTA at final trial visit)
- Urine protein / creatinine ratio (required for all patients at this visit)
- Urine storage

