## 7.3 Procedures for assessing safety

A symptom evaluation and targeted physical examination will be performed at each visit.

Body composition changes will be evaluated at baseline, annual visits and the final study visit as follows:

- Waist circumference will be measured between the lower border of the ribs and the iliac crest, in a horizontal plane.
- Hip circumference will be measured at the widest point over the buttocks.
- Patients will be asked about any change in fat in the face, arms, legs or abdomen. Taking into account the patient's opinion, the research nurse or doctor will grade facial lipoatrophy as none, moderate (evident on inspection), or severe (immediately obvious).

Patients will be asked about symptoms of peripheral neuropathy at baseline, annual visits and the final study visit. A brief neuropathy examination will be performed at baseline and the final study visit in all patients, and at intervening annual study visits if the patient reports neuropathy symptoms

Cardiovascular risk factors will be assessed at annual trial visits, and risk will be quantified using the Joint British Societies cardiovascular risk prediction charts (see Appendix 11).

Blood will be drawn at trial visits to assess laboratory safety parameters according to standard-of-care as indicated in the schedule of trial assessments (see section 1.3). Additional safety blood tests or investigations will be performed to investigate symptoms or monitor emergent laboratory test abnormalities as clinically indicated.

All adverse events will be reported on the case report form. Adverse events (clinical and laboratory) will be graded using the 2004 Division of AIDS toxicity grading scale (see Appendix 7). Serious adverse events will be defined according to the EU Directive 2001/20/EC Article 2 based on ICH GCP, and will be reported to the MRC CTU for the duration of the main trial i.e. whilst patients are attending trial visits according to standard timelines (see section 11).

Diagnostic criteria for selected serious AIDS and non-AIDS events are defined in the protocol (see section 9.2.2 and Appendices 8 and 9), and sites will be encouraged to investigate patients in a way that allows determination of whether patients meet the specified diagnostic criteria. An independent endpoint review committee will review these endpoints to ensure that they satisfy the criteria.

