#### 9.2.2 Secondary outcome measures

- **Serious drug or disease-related complication**

Defined as the first occurrence of one of the following in any individual patient:

- **Death from any cause**
- **Serious AIDS-defining illness** (see diagnostic criteria, Appendix 7)
- **Serious non-AIDS defining illness** (see diagnostic criteria, Appendix 8)
  - Acute myocardial infarction
  - Coronary artery disease requiring invasive procedures
  - Cirrhosis
  - Acute liver failure
  - End-stage renal disease
  - Stroke
  - Clinical acute pancreatitis
  - Severe lactic acidemia
  - Severe facial lipoatrophy
  - Severe peripheral neuropathy
  - Non-AIDS malignancy

- **Adverse events**

Defined as the total number of Grade III and IV adverse events.

- **Confirmed Virological rebound**

Defined as 3 consecutive VL tests  $\geq 50$  copies/ml, with at least 4 weeks between the first and last test. One of these 3 tests may be a repeat of the same sample. There are a number of alternative definitions for virological rebound, each of which has advantages and limitations (28). The alternative definitions to be used in this trial will be described in the full statistical analysis plan.

- **CD4+ count change**  
Defined as change from baseline in absolute CD4+ count.
- **Health-related Quality of Life change**  
Defined as change from baseline in the mental and physical health summary scores.
- **Neurocognitive function change**  
Defined as change from baseline in the neurocognitive function summary score.
- **Cardiovascular risk change**  
Defined as change from baseline in the risk of cardiovascular disease calculated from the Framingham equation (19).
- **Health care costs**  
Defined as the total cost of health care resources utilised per patient year.

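### Calcium and phosphate are tested every 12 weeks only in patients taking tenofovir, which the PI arm stops, so Grade III/IV events for these two analytes are more likely to be detected in control

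*Combined protocol and SAP*

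**What the plan says.** Patients in both arms are seen "with 12-weekly visits throughout the trial" (section 7.1). Calcium and phosphate are taken from everyone at Week 12 (7.1.3) and at the annual and final visits, where section 7.1.5 has "Bone profile (calcium and phosphate; required for all patients at this visit". At the other 12-weekly visits, section 7.1.4 has "Bone profile (calcium and phosphate; only required for patients taking tenofovir". Footnote 4 of the Trial schedule (1.3) states the same rule: "annual visits in all, but quarterly only in those patients taking tenofovir".

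Under section 6.3.1 the PI arm ends up on a single ritonavir-boosted PI. The two NRTIs stop at once in patients entering on a PI-based regimen, and after two weeks in those entering on an NNRTI-based one. Tenofovir is not among the PIs listed in Appendix 9, so it stops in this arm.

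Section 7.3 states: "Adverse events (clinical and laboratory) will be graded using the 2004 Division of AIDS toxicity grading scale". Appendix 6 sets Grade 3 and 4 limits for low phosphate and for high and low calcium. The adverse event outcome in section 9.2.2 reads: "Defined as the total number of Grade III and IV adverse events". Section 9.5.2 tabulates these events by body system and arm and compares the arms with a chi-squared test. Neither section restricts the comparison to visits that all patients share, or allows for the number of tests.

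**The concern.** Objective 2 (section 2.4.1) is to compare safety and toxicity between the strategies, and section 2.5.5 names less long-term toxicity from stopping NRTIs as a possible benefit of PI monotherapy. If one arm is tested more often for an analyte, short-lived abnormalities of that analyte will be recorded more often there even when the true rates are equal. Here the testing frequency is a consequence of randomisation. A Grade III phosphate at week 60 that had resolved by week 96 would be an event in a control patient on tenofovir and would go unseen in a PI-arm patient who had stopped it. For these two analytes, a lower count in the PI arm could not be separated from less frequent measurement.

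**Working it through.** The plan gives no testing-frequency figure to reproduce, so the check counts scheduled tests.

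**Inputs.** Visits every 12 weeks (7.1). All-patient tests at Week 12, Weeks 48, 96, 144, 192 and 240, and the final visit (7.1.3, 7.1.5). Accrual over 24 months and total duration of 60 months (9.3), so follow-up of 36 to 60 months, about 156 to 260 weeks. Footnote 9 of the schedule says: "The final visit will be scheduled within 12 weeks before the common closing date of the trial". The final visit is therefore placed at the last 12-weekly visit. No scheduled calcium or phosphate test falls in the two weeks when some PI-arm patients still take NRTIs.

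**Tests per patient after randomisation**

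| Follow-up (weeks) | On tenofovir | Not on tenofovir | Ratio |
|---|---|---|---|
| 156 | 13 | 5 | 2.60 |
| 192 | 16 | 5 | 3.20 |
| 208 | 17 | 6 | 2.83 |
| 240 | 20 | 6 | 3.33 |
| 260 | 21 | 7 | 3.00 |

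At 208 weeks the 6 are Weeks 12, 48, 96, 144, 192 and the final visit. At 240 weeks the final visit coincides with the Week 240 annual visit.

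**Arm-level ratio at 208 weeks.** Let s be the share of control patients on tenofovir (assumed, as the documents do not give it) and r the share of PI-arm follow-up back on tenofovir. The ratio is [17s + 6(1 − s)] / [17r + 6(1 − r)].

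- r = 0, s = 0.4: 10.4 / 6 = 1.73
- r = 0, s = 0.6: 12.6 / 6 = 2.10
- r = 0, s = 0.8: 14.8 / 6 = 2.47
- s = 0.6, r = 0.10: 12.6 / 7.1 = 1.77
- s = 0.6, r = 0.15: 12.6 / 7.65 = 1.65

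The cases with r above 0 reflect section 6.3.6, under which PI-arm patients who resume triple therapy normally return to their entry regimen.

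**All graded scheduled blood tests, 240 weeks.** Ten analytes are measured at every 12-weekly visit in everyone: haemoglobin, white cells, neutrophils, platelets, sodium, potassium, creatinine, bilirubin, ALT and alkaline phosphatase. Four (glucose, cholesterol, LDL, triglycerides) follow the Week 12, annual and final schedule. The PI arm alone has one extra round of these fourteen at Week 4.

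- PI arm: 10 × 21 + 2 × 6 + 4 × 7 = 250
- Control, s = 0.5: 10 × 20 + 2 × 13 + 4 × 6 = 250, ratio 1.00
- Control, s = 1: 10 × 20 + 2 × 20 + 4 × 6 = 264, ratio 1.06

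For s from 25% to 100% and follow-up of 156 to 260 weeks, this overall ratio runs from 0.94 to 1.06.

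**The case against.** Most safety bloods follow the same 12-weekly schedule in both arms, and over all graded analytes the scheduled tests differ by about 6% at most, in either direction. The PI arm also has tests of its own: blood count, biochemistry, fasting glucose and lipids at Week 4 (7.1.1). Footnote 5 of the schedule allows extra lipid tests if Week 12 lipids are raised. Creatinine is measured quarterly in everyone, and the other tenofovir-triggered test, the urine protein/creatinine ratio, has no grade in Appendix 6. A persistent abnormality would be found at the next annual visit anyway, so more tests do not mean proportionally more events. Section 9.5 leaves a full analysis plan still to be written.

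All of this stands, and it limits the point. A reader might infer that control patients in general have about three times the chance of recording any Grade III/IV laboratory event, or that the whole toxicity comparison is tilted towards PI monotherapy. The documents support neither: the ratio concerns control patients on tenofovir and two analytes, and without event rates per analyte the net direction is unknown. A larger ratio, such as 17 to 5 = 3.4 at 208 weeks, appears only if the all-patient final visit is left out.

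The objection does not remove the imbalance. Section 9.5.2 tabulates by body system, so the excess calcium and phosphate testing falls in particular rows and is not diluted over some 250 tests per patient. The Week 4 bloods concern other analytes and cannot offset it there.

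**Conclusion.** The point holds for calcium and phosphate. Following the plan as written, Grade III/IV events for these two analytes are more likely to be detected in control, which favours PI monotherapy for those events. Control patients on tenofovir have between 2.6 and 3.3 times as many scheduled tests at the follow-up lengths tabulated. At arm level the 208-week ratio is 1.73 to 2.47 if 40% to 80% of control patients take tenofovir and none of the PI arm does. It is about 1.65 to 1.77 at 60% if 10% to 15% of PI-arm follow-up is back on the drug. These shares are assumptions. The ratios count tests, and are upper bounds on the event ratio that would arise with no true difference. The mechanism is certain from the documents; the size is not. It affects one component of one secondary outcome.

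**What to change.** In section 9.5.2, and in the full analysis plan before the trial is analysed, state that the between-arm comparison of Grade III/IV events counts calcium and phosphate events only from tests at Week 12, annual and final visits. An abnormality first seen on an extra test and still Grade III or IV at one of those visits then counts from that visit. List events found only on the extra tenofovir-triggered tests separately, by arm, as safety data. The scheduled calcium/phosphate test ratio between arms becomes 1.0.

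Keep the PI arm's Week 4 laboratory events in the main comparison and show the result without them as a sensitivity analysis. Removing them from the main result would discard early toxicity in patients newly started on a PI, which would itself favour that arm.

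The cost is analysis wording. Clinical monitoring, visits and tests are unchanged. The downside is that a few calcium and phosphate events leave the formal comparison.
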